## Abstract

**Background:**

Breast cancer survivors often encounter physiological and psychological problems related to their diagnosis and treatment that can influence long-term prognosis. The aim of this research is to investigate the effects of a lifestyle intervention on body weight and psychological well-being in women recovering from breast cancer treatment, and to determine the relationship between changes in these variables and biomarkers associated with disease recurrence and survival.

**Methods/design:**

Following ethical approval, a total of 100 patients will be randomly assigned to a lifestyle intervention (incorporating dietary energy restriction in conjunction with aerobic exercise training) or normal care control group. Patients randomised to the dietary and exercise intervention will be given individualised healthy eating dietary advice and written information and attend moderate intensity aerobic exercise sessions on three to five days per week for a period of 24 weeks. The aim of this strategy is to induce a steady weight loss of up to 0.5 Kg each week. In addition, the overall quality of the diet will be examined with a view to (i) reducing the dietary intake of fat to ~25% of the total calories, (ii) eating at least 5 portions of fruit and vegetables a day, (iii) increasing the intake of fibre and reducing refined carbohydrates, and (iv) taking moderate amounts of alcohol. Outcome measures will include body weight and body composition, psychological health status (stress and depression), cardiorespiratory fitness and quality of life. In addition, biomarkers associated with disease recurrence, including stress hormones, estrogen status, inflammatory markers and indices of innate and adaptive immune function will be monitored.

**Discussion:**

This research will provide valuable information on the effectiveness of a practical, easily implemented lifestyle intervention for evoking positive effects on body weight and psychological well-being, two important factors that can influence long-term prognosis in breast cancer survivors. However, the added value of the study is that it will also evaluate the effects of the lifestyle intervention on a range of biomarkers associated with disease recurrence and survival. Considered together, the results should improve our understanding of the potential role that lifestyle-modifiable factors could play in saving or prolonging lives.

## Background

Although the number of women who survive breast cancer is increasing, survivors often encounter physiological and psychological problems related to their diagnosis and treatment that can influence long-term prognosis. A gain in body weight [1-6] and psychosocial distress [7-12] are two commonly encountered adverse responses to breast cancer diagnosis and treatment that can have a negative impact on quality of life and survival. Lifestyle strategies that can attenuate the negative effects of such physical and mental health outcomes after breast cancer diagnosis could further improve the quality of life and long-term prognosis of breast cancer survivors.

Up to 60% of women diagnosed with breast cancer experience an increase in body weight associated with chemotherapy and treatment-related menopause [6] and there is evidence that heavier women and women who gain weight after diagnosis have an increased risk of disease recurrence and death compared to normal weight women [1-5]. Women with a high body mass index (BMI) have double the risk of 5-year recurrence and a 60% increased risk of death over 10 years in comparison to normal-weight women [5]. Poorer survival in heavier patients could be due to higher levels of tumor-promoting hormones, consequent to an increased adiposity [13]. There is evidence that elevated estrogen levels influence the risk of breast cancer in postmenopausal women [14-16] and it was recently shown that overweight postmenopausal breast cancer patients have higher estrogen and testosterone levels than normal-weight patients [13]. This led to the suggestion that circulating estrogen levels could be a useful biomarker for weight loss intervention studies [13].

Following breast cancer diagnosis or treatment, four in ten women also experience high levels of emotional distress, including depression and anxiety [7], which persists for prolonged periods of time, irrespective of the treatment outcome [8-12]. Studies have shown that psychosocial stressors such as depression, anxiety and emotional distress are associated with impaired immune function [17], and this could have a direct impact on cancer outcomes [18,19] and influence the risk of disease re-occurrence and death [20]. The adverse effect of psychosocial stressors on immune function is considered to be mediated by excess secretion of the stress hormone cortisol and the catecholamines [21,22]. Elevated cortisol and catecholamine levels evoked by psychological stressors can significantly influence immune function, including lymphocyte proliferation and natural killer (NK) cell activity [23-26]. Self-reported negative mood states have been associated with lower NK cell activity [27,28] and symptoms of depression have been linked with increased salivary cortisol [29] impaired lymphocyte proliferation [30,31] and reduced NK cell cytotoxicity against tumor cells [32-34]. In addition, studies have reported abnormal circadian rhythmicity of cortisol in breast cancer patients [35-39] and flattened or abnormal diurnal salivary cortisol rhythms have recently been associated with earlier mortality in breast cancer patients [38] and persistent fatigue in survivors 1–5 years after initial diagnosis [40].

Dietary energy restriction can reduce body weight and induce a positive effect on psychological well being in obese women and breast cancer survivors [41-44]. Weight loss interventions that reduce dietary intake of fat to 18–25% of the total calories can also evoke a significant reduction in serum estrogen levels in pre and postmenopausal women [45]. The positive effects of dietary energy restriction on these physical and emotional sequelae might be augmented by the implementation of adjunctive exercise therapy [46,47]. Regular physical activity can help to control body weight and is known to reduce the risk of breast cancer [48-53]. Recent evidence also suggests that it can halve the risk of death in breast cancer patients [54]. The precise mechanisms underpinning the positive effects of physical activity on breast cancer risk and survival are unknown, although physical activity has been associated with a lower concentration of circulating estrogen in some studies [55,56], as well as lower circulating levels of the inflammatory mediators, C-reactive protein (CRP) [57-59] and interleukin-6 (IL-6) [60,61]. Increased CRP levels are observed in overweight individuals [62,63] and have been linked with increased cancer risk [64,65] and elevated levels of cortisol in individuals subjected to psychological stress [66]. Depression enhances the production of IL-6 [67-69] and this proinflammatory cytokine is also secreted from adipocytes in proportion to body fat mass [60]. IL-6 induces CRP synthesis in the liver and can indirectly raise cortisol levels via stimulation of corticotropin-releasing hormone production [67]. Elevated estrogen levels may also increase CRP levels through a non-inflammatory mechanism [70].

Regular physical activity can also have a positive effect on psychological health status [71,72] and quality of life [73] in breast cancer survivors that could enhance immune function through normalisation of stress hormone levels. Although there is evidence for decreased cortisol levels [74,75] and changes in immune cell numbers and function after psychosocial interventions in breast cancer patients [76,77], only three studies have investigated the effects of exercise therapy on immune function in breast cancer survivors. Peters *et al*. [78,79] reported an increase in the percentage of NK cells and an improvement in NK cell function and monocyte phagocytic capacity that was accompanied by an increase in 'satisfaction of life' score after seven months of moderate exercise training, whereas Nieman *et al*. [80] did not observe any change in NK cell function following a shorter period of training. The latter study had only six subjects in the experimental (exercise therapy) group, and neither study measured stress hormone levels in patients. In a more recent study, Fairey *et al*. [81] showed that a 15 week programme of aerobic exercise training improved NK cell cytotoxic activity and peripheral blood lymphocyte function in postmenopausal breast cancer survivors. In sedentary, healthy individuals, regular moderate aerobic exercise has been shown to boost NK cell function [82] and decrease the incidence of upper respiratory tract infections in previously sedentary individuals [82-84]. In elderly females however, evidence for an improvement in immune cell function with aerobic exercise training is inconclusive, although highly trained elderly females exhibit superior resting NK cell function and T cell proliferation responses compared to age-matched sedentary controls [83]. The lack of intervention studies incorporating biomarkers of immune function in women recovering from breast cancer treatment is surprising, as restoration of lymphocyte and NK cell function after treatment is predictive of survival [28,85,86] and is independent of stage of disease and adjunctive treatment approach [86]. This suggests that lifestyle interventions which could have an impact on immune function are worth exploring, as they could have a significant influence on disease-free survival in breast cancer patients.

Previous studies have investigated the feasibility and efficacy of lifestyle interventions in breast cancer patients and obese women, in terms of recruitment, compliance and weight loss [42,43,87,88]. Some studies have also examined the effects of lifestyle interventions on aspects of psychological [41,47,71,72] and physiological [42,87,88] well-being. However, no previous studies have investigated the effects of a dietary and exercise intervention on a range of important prognostic breast cancer biomarkers that could be strongly influenced by weight loss and improved psychological well-being. Thus, the aim of the intended research is to examine the effects of a dietary and exercise intervention on body weight, indices of psychological well-being and biomarkers associated with disease recurrence and physiological health status in female breast cancer survivors. We hypothesize that the lifestyle intervention will evoke a reduction in body weight and an improvement in psychological well-being. Secondly, that improvements in blood markers of cancer risk and physiological health status (estrogen, CRP, IL-6), psychosocial stress (cortisol and catecholamines) and immune function (lymphocyte proliferation and NK cell function) will be associated with changes in body weight and psychological well-being induced by the lifestyle intervention. Considered together, the results of this study would provide valuable new information to improve our understanding of the role that lifestyle-modifiable factors can play in saving or prolonging the lives of women who have been treated for breast cancer.

## Research design and methods

### Overall aim of the study

To examine the effects of a practical lifestyle intervention that could be easily implemented by overweight or obese women (BMI > 25) who have undergone breast cancer treatment, on body weight, indices of psychological well-being, biomarkers associated with disease recurrence and physiological health status and quality of life.

### Primary aims

1. To examine the effects of a dietary and exercise intervention on body weight and body composition in overweight or obese women who have undergone breast cancer treatment.

2. To examine the effects of a dietary and exercise intervention on indices of psychological health status and biomarkers associated with disease recurrence in overweight or obese women who have undergone breast cancer treatment.

### Secondary aims

1. To examine the relationship between change in body weight and biomarkers associated with disease recurrence and physiological health status, including circulating levels of estrogen, CRP and IL-6.

2. To examine the relationship between changes psychological health status, circulating stress hormones and indices of immune function.

3. To examine the effects of the dietary and exercise intervention on broader quality of life dimensions.

### Patient recruitment

A total of 100 women (BMI > 25) who have undergone appropriate treatment for operable breast cancer within the past 3–18 months and are no longer undergoing chemotherapy or radiation therapy, will be recruited from the Cancer Research Centre, Weston Park Hospital, Sheffield University Hospitals NHS Trust. The incidence of breast cancer within the North Trent Regional Health Authority area is relatively high, with 850 cases per year and, on the basis of current rates of breast cancer survival in South Yorkshire and recruitment rate in our ongoing trial, we expect to recruit patients at the rate of approximately six per month for 16 months. Ethical approval has been obtained from the South Sheffield Research Ethics Committee and informed consent will be obtained from all participants before they enter the study.

### Randomisation

The minimisation technique [89] will be used to allocate the patients into one of two groups (i) lifestyle intervention group, incorporating moderate dietary energy restriction of 600 kcal per day in conjunction with aerobic exercise training on 3–5 days per week, or (ii) normal care control group. Minimisation will be used to balance the potentially confounding variables of chemotherapy and treatment with Tamoxifen, aromatase inhibitors or no hormone therapy across the groups. Randomisation will be performed by an independent researcher at the Clinical Trials Research Unit, University of Leeds. The intervention will last for 24 weeks, with outcome measures being assessed in the week before and the week after the intervention period and at the mid-intervention time point of 12 weeks. Patients would be recruited over 16 months, ensuring completion of the trial by 22 months and reporting of the data by 24 months.

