### Details of power calculations and sample size

Body weight was chosen as the primary outcome variable for calculation of sample size. Utter *et al*. [88] reported a 8.1 kg reduction in body weight in obese women following a 12 week lifestyle intervention, incorporating moderate dietary energy restriction in conjunction with exercise. Body weight changed from a baseline ± SD level of 89.9 ± 11.7 to 81.8 ± 10.8 kg following the intervention. This amount of weight loss is associated with improved physical and psychological health in obese women [41,90]. On the basis of these data, and taking into account an expected patient drop-out of up to 10% (based on the drop-out rate in our ongoing trial with breast cancer survivors [91]), recruitment of 50 patients for each group will give us 90% power to detect a difference in body weight of 8 kg at the α level of 0.05.

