### Patient inclusion criteria

a. Postmenopausal women (confirmed by plasma estradiol and gonadotrophin measures in all women aged <55) with a BMI > 25 and classified as disease stage I-III. In our experience [91], a high proportion of breast cancer patients (>80%) meet the BMI criteria and would be suitable for participation in the study.

b. Patients must have completed some form of breast cancer treatment at least three months, and not more than 18 months ago.

c. Patients on Tamoxifen and other endocrine treatments but not hormone replacement therapy (HRT) will be included.

d. Patients must be willing and able to attend supervised exercise sessions at least 3 times per week for a period of 24 weeks, with the intention of achieving an 80% minimum compliance target for attendance.

e. Patients must be an exercise pre-contemplator, contemplator or preparer as defined by the Transtheoretical Model [92].

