##### Estrogen, stress hormones and inflammatory markers

Plasma IL-6, epinephrine and norepinephrine levels will be measured using commercially available enzyme-linked immunoassays (ELISA) kits (Bio-Quant Inc and Immunobiological Laboratories, Hamburg, R & D Systems UK) and plasma hs-CRP will be measured by the Immunology Department, Northern General Hospital, Sheffield using a turbidimetric assay. Serum estradiol, estrone and estrone sulphate will be measured using high-sensitivity ELISA kits Bio-Quant Inc., CA, USA and Diagnostic Systems Laboratories Inc., OBI-DSL, Oxon, UK). Salivary cortisol levels will be measured on each of three consecutive days at 0800, 1200, 1700 and 2100 hours and the slope of diurnal cortisol variation will be determined from the pooled saliva samples at each daily time point using a regression of the log-transformed cortisol concentrations on sample collection time [38]. Easy-Reach Radio Pagers (British Telecommunications Plc, UK) will be used to signal saliva collection times and the importance of collecting samples at the designated times and recording the actual sample collection time will be emphasized. Saliva samples will be refrigerated, before collection within 2–4 days and frozen at -70°C until analysis[40] using a high sensitivity salivary cortisol enzyme immunoassay (Salimetrics LLC, PA, USA).

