### Data Analysis

A mixed factorial ANOVA will be used to assess (i) changes from baseline on all outcome measures following the intervention within patient groups, and (ii) differences in outcome measures between patients in the lifestyle intervention and control groups post intervention. Pearson product moment correlation coefficients (r) will be calculated to determine bivariate relationships among changes in the variables. Statistical significance will be set at *p *< 0.05. All data will be analysed using the SPSS statistical package (SPSS UK Ltd, Woking, U.K.).

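### The minimisation factors (chemotherapy, endocrine therapy) are absent from the stated analysis model, so the between-group post-intervention comparison is somewhat conservative; adding them costs little

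*Protocol article*

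**What the plan says.** The Randomisation section allocates by minimisation and gives the reason: "Minimisation will be used to balance the potentially confounding variables of chemotherapy and treatment with Tamoxifen, aromatase inhibitors or no hormone therapy". The inclusion criteria ensure that endocrine therapy varies within the trial: "Patients on Tamoxifen and other endocrine treatments but not hormone replacement therapy (HRT) will be included".

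The Data Analysis section gives one model for all outcomes: "A mixed factorial ANOVA will be used to assess (i) changes from baseline on all outcome measures following the intervention within patient groups". Its second part covers "differences in outcome measures between patients in the lifestyle intervention and control groups post intervention". Pearson correlations among changes follow. No covariate is named there, and no other section brings chemotherapy or endocrine therapy into the analysis.

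The outcomes include hormones that endocrine therapy may affect: "Serum estradiol, estrone and estrone sulphate will be measured using high-sensitivity ELISA kits". The sample size section rests on body weight and claims "90% power to detect a difference in body weight of 8 kg at the α level of 0.05".

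**The concern.** The plan treats the two factors as important enough to constrain allocation, then states an analysis that ignores them. Balancing a prognostic factor removes its contribution to the chance difference between groups. If the model omits the factor, that variance stays in the error term. The reported standard error then exceeds the true one, confidence intervals are too wide and p-values too large.

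What is at stake is precision. A real post-intervention difference could be missed, or reported with more uncertainty than the design warrants, although the information needed to avoid this is already collected for allocation.

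**Working it through.** **Inputs from the protocol article.** 50 recruited per group; drop-out up to 10%, so 45 completers per group; difference 8 kg; baseline SD 11.7 kg; α 0.05 (two-sided assumed, as sidedness is not stated).

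**Input not in the article.** R², the share of outcome variance explained by the minimisation factors, is assumed and shown as a range.

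**1. The plan's own figure.** The standard error of the difference is 11.7 × √(2/45) = 2.467 kg. Then 8/2.467 = 3.243, and power = Φ(3.243 − 1.960) = 90.0%. The required number is 45 per group, and 45/0.90 = 50. The stated calculation reproduces as an unadjusted two-sample comparison.

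**2. Effect of omitting balanced factors.** With perfect balance, the true variance of the group difference is (1 − R²) times the variance that the unadjusted model uses. Hence, for an effect set at nominal 90% power (1.96 + 1.2815 = 3.2415):

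- reported SE / true SE = 1/√(1 − R²)
- real type I error = 2Φ(−1.96/√(1 − R²))
- real unadjusted power = Φ(1.2815/√(1 − R²))
- adjusted power = Φ(3.2415/√(1 − R²) − 1.96)

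| Assumed R² | SE ratio | Real type I error | Unadjusted power | Adjusted power |
|---|---|---|---|---|
| 0.05 | 1.026 | 4.4% | – | – |
| 0.10 | 1.054 | 3.9% | 91.2% | 92.7% |
| 0.20 | 1.118 | 2.8% | 92.4% | 95.2% |
| 0.30 | 1.195 | 1.9% | 93.7% | 97.2% |

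The power gain from adjustment is therefore about 1.5, 2.8 and 3.5 points at R² of 0.10, 0.20 and 0.30. Unadjusted power is itself above 90%, because the balance helps even when the model ignores it.

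**3. Body weight.** The 95% confidence interval half-width is 1.96 × 2.467 = 4.83 kg unadjusted. Multiplied by √(1 − R²), it becomes 4.79 kg at R² 0.02, 4.71 kg at 0.05 and 4.59 kg at 0.10.

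**4. Simulation with imperfect balance.** Minimisation on two factors was simulated with N = 100, 10% drop-out, no treatment effect, 3,000 replicates and factor effects stable over time. The factor frequencies and the within-patient correlation (0.6 after removing the factors) were assumed.

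| Analysis | R² 0.05: SE ratio, type I | R² 0.30: SE ratio, type I | R² 0.60: SE ratio, type I |
|---|---|---|---|
| Post value, unadjusted | 1.025, 4.4% | 1.181, 1.8% | 1.423, 0.6% |
| Post value, factors added | 1.005, 4.7% | 1.003, 4.6% | 0.976, 5.6% |
| Change, unadjusted | 1.026, 4.3% | 1.040, 4.3% | 1.001, 5.1% |
| Change, factors added | 1.026, 4.4% | 1.041, 4.1% | 1.000, 5.1% |

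For the post-intervention value, adding the factors restores the SE ratio to about 1 and type I error to about 5%. For change, adding them makes no material difference: a stable factor effect is present at both times and subtracts out.

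**5. Adding the baseline value.** At R² 0.30 the mean standard error (in outcome SD units) was 0.211 unadjusted, 0.177 with the factors, 0.147 with baseline only and 0.142 with both. Under these assumptions baseline brings the larger gain, and the factors add a little more.

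**The case against.** The strongest objection is that silence is being read as exclusion. Data Analysis is a short paragraph in a journal article, and covariate terms are commonly left to a statistical analysis plan, which is not shown. That plan may add the factors. This limits the point but does not remove it: the article names a specific model, applies it to all outcomes and does not defer its terms, so following it as written gives the result above.

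A second objection is that the harm is small. This largely stands. There is no bias and no excess of false positives, and for body weight the loss is probably slight.

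A third objection is that the group-by-time test in a mixed ANOVA is within-patient, so stable factor effects cancel. This also stands. It confines the point to the between-group post-intervention contrast that Data Analysis names separately.

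A reader might go further on estrogen and infer that its type I error is about 0.6%, or that the pooled effect is diluted because women on aromatase inhibitors cannot respond and should leave the main analysis. The documents do not support this. They give no R², no share of aromatase inhibitor users and no statement about how estrogen changes in those women. The 0.6% figure needs an R² of 0.50 or more and applies only to the post-intervention value. Estrogen is named in secondary aim 1; primary aim 2 refers to recurrence biomarkers only in general terms. Dropping aromatase inhibitor users would change the population that the trial chose to enrol.

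**Conclusion.** The point holds as a modest loss of precision. For the between-group post-intervention comparison, the stated analysis gives standard errors that are too wide to the extent that chemotherapy and endocrine therapy predict the outcome: about 1% to 5% too wide at R² of 0.02 to 0.10, and about 18% to 20% at 0.30. It could matter more for post-intervention estrogen levels than for body weight, but the article does not allow that to be quantified. For change scores or the group-by-time test it is near nil if the factor effects are stable.

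The direction follows from the design; every size rests on an assumed R² and, in the formulas, on perfect balance. Nothing here shows the sample size to be wrong or the trial's conclusions to be at risk of false positives. It is an improvement worth making, not a flaw in validity.

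**What to change.** Add to Data Analysis a sentence such as: *Between-group comparisons will include chemotherapy (yes/no) and endocrine therapy class (Tamoxifen, aromatase inhibitor, none) as fixed effects, together with the baseline value of the outcome.* The article does not give the levels used for chemotherapy, so the levels should match those used in the minimisation.

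Estrogen results by endocrine therapy class may be reported as a supportive analysis, with all randomised women kept in the main analysis.

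The cost is 3 degrees of freedom for the factors (1 + 2) and 1 for baseline, out of about 90 completers. The factors are already recorded for allocation, so no new data are needed. The change should be made before outcome data are seen.
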